## Methods: participants, interventions, and outcomes

### Study setting {9}

The trial will be conducted in Yibin city, Sichuan province, China. Yibin is a midsize city located in the joint region of Sichuan, Yunnan, and Guizhou province. Given its population, location, economy, and living standard of people, Yibin can represent the central region of China to a certain extent [26]. Therefore, hypertensive patients in Yibin are representative in terms of demographic characteristics and technology acceptance. In this trial, the participating physicians (cardiologists) are recruited from the First People’s Hospital of Yibin, which is a tertiary hospital with four major districts (A, B, C, and D). A well-equipped health management center (HMC) is established in B district cooperating with ZICT Technology Co., Ltd. (ZICT). The patient enrolment and outcome measurements will be performed in the HMC. The participating GPs and CMs are from 3 community health centers near the First People’s Hospital of Yibin.

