### Sample size {14}

The power calculation is based on the primary outcome measure and aims for a mean systolic blood pressure variation of 5 mmHg with a standard deviation of 16.5 mmHg (the effect size is based on a previous study [29]). Assuming an α of 5%, and power of 0.80, 171 patients per group are required at the end of the trial (342 in total). Considering an attrition percentage of 15%, our aim is to include a minimum of 402 patients at baseline.

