#### Work efficiency of care providers

Work efficiency of care providers will be calculated based on the follow-up data. In this trial, all the follow-ups are generated, conducted, and recorded through the system. The generated follow-up requests can be divided into 3 types: regular follow-up, abnormal attention follow-up, and compliance follow-up. The system needs to schedule all the follow-ups reasonably to make care providers handle requests timely. We propose 2 indexes to assess the work efficiency: one is the frequency of follow-up in a day, which demonstrates how our system reduces the time cost of a single follow-up; another one is the handling time of a follow-up request, which means the time duration before a generated follow-up request is handled. Intuitively, the more follow-up care providers conduct in a day and the less handling time a follow-up request costs, the more effective their work will be. We will derivate the average work efficiency of care providers in the entire trial period for the control group and the intervention group, respectively. For the handling time of a follow-up request, we will calculate time cost for the 3 types of follow-ups respectively, then sum it together with different weights to get the average time cost.

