## Statistical methods

### Statistical methods for primary and secondary outcomes {20a}

Statistical analysis will be performed using SPSS version 23.0. All statistical tests will be reported as a two-sided significance level of 5%, and the results will be presented with two-sided 95% confidence intervals (CIs). The data will be treated either by parametric or non-parametric analysis based on the tests for normal distribution (Shapiro-Wilk test) and homoscedasticity (Levene’s test). We will first conduct detailed exploratory descriptive analyses to collected data using graphical and numerical summaries. Then, comparisons between and within groups will be performed to identify the effectiveness. For categorical variables, the Pearson chi-square test or Fisher exact test will be used; for continuous variables, the Student *t* test or Mann-Whitney test will be used. In case of significant baseline differences, a linear mixed model will be constructed for the outcomes adjusting the baseline using the following covariates as appropriate: baseline SBP, demographics (age, gender, education levels), and BMI. Only those confounding factors found to be statistically significant to the outcomes by analysis of covariance will be included in the final model.

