## Discussion

This protocol has been designed to understand the effectiveness of a pathway-driveneHealth-based integrated care model, implemented as a full-featured telehealth system. Compared with prior studies [38, 39], our study innovatively introduces the concept of pathway, then combines it with information technology and the “three-manager” mode to establish a standardized and executable care model. Besides testing efficacy of the model, this study will have several other strengths if successful. First, the model can be generalized to other common chronic diseases, such as diabetes, stroke, and chronic obstructive pulmonary disease (COPD). The task-based pathway can be applied in both single disease and multiple chronic conditions. Second, the study would provide the feasibility evidence of the “three-manager” mode combined with information technology in China. Policy makers in other regions across the country could roll out similar services for better management. Last, the awareness, treatment, and control rates of hypertension in Sichuan, Yunnan, and Guizhou are relatively low compared with other provinces [40]. Therefore, performing such a trial in Yibin is significant to improve the local outcome for hypertension management.

The present protocol is also subject to some limitations. First, since the clients for patients are different from traditional mobile applications, participants may show different levels of acceptance in the system. Low system acceptance will lead to undesirable high attrition rates. We will adopt several strategies to improve patients’ acceptance of the system, including ongoing system updates with usability tests, online system guidance from CMs, and regular offline training sessions for patients. Second, this is an open-label trial for both patients and care providers. Patients in the control group may not comply with self-management regimes or even choose to discontinue the participation, and care providers may tend to conduct the management for the control group not following the guidelines. We plan to eliminate these potential biases through intensive training of care providers and reward mechanism on patients (for example, free outpatient registration), as well as supervision of intervention quality from the steering committee.

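### The plan's general independent-sample tests also cover work efficiency of care providers, where the data are clustered by patient and provider and probably paired by provider across arms

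*Protocol article*

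**What the plan says.** The abstract lists work efficiency of care providers among the secondary outcomes, and Outcomes {12} has it assessed at 12 months to validate the model from the provider side. Under Work efficiency of care providers, two indexes are defined from the system log: follow-ups conducted in a day, and the time until a follow-up request is handled. For both, "We will derivate the average work efficiency of care providers in the entire trial period for the control group and the intervention group, respectively". Handling time is computed separately for regular, abnormal-attention and compliance follow-ups and then combined with weights.

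Statistical methods for primary and secondary outcomes {20a} says that "comparisons between and within groups will be performed to identify the effectiveness", and gives the Student t or Mann-Whitney test for continuous variables. A linear mixed model appears there only for the case of baseline differences. Its listed covariates are all patient characteristics, with no provider or center term.

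On staffing, Study setting {9} says: "The participating GPs and CMs are from 3 community health centers". No head count is given. Patients are randomized individually by envelope (Implementation {16c}). In Table 1, GPs perform the regular follow-ups in both arms. The Discussion names as a risk of the open-label design that "care providers may tend to conduct the management for the control group not following the guidelines".

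**The concern.** A two-sample t or Mann-Whitney test needs independent observations within and between arms. Work efficiency does not supply them. One patient generates several requests in a year, and one GP or CM handles many requests. If the same GP or CM handles requests from both arms, that person's two averages are also correlated.

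The general rule does not fix the unit, and the consequences run in opposite directions. Treating each request as independent can give standard errors that are far too small. Treating each provider's two averages as coming from different people gives standard errors that are too large.

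The conditional mixed model offers no way out. Work efficiency is assessed only at 12 months, so it has no baseline to trigger the model, and the model names no provider term. At stake is the trial's only provider-side evidence, not its primary result.

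**Working it through.** **The plan's own figure.** The only calculated size is for systolic blood pressure; it "aims for a mean systolic blood pressure variation of 5 mmHg with a standard deviation of 16.5 mmHg". With two-sided α 0.05 and power 0.80, n = 2 × (1.960 + 0.842)² × 16.5² / 5² = 170.95, so 171 per group and 342 in total. Then 342 / 0.85 = 402.35, against the planned 402. The figure reproduces. It has no bearing on work efficiency, for which no size is given.

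**Inputs from the article.** 402 / 2 = 201 patients per arm. Regular follow-up in Table 1 runs from every 3 months (4 a year) to every 4 weeks (about 13) or every 2 weeks (about 26). That is 201 × 4 = 804, 201 × 13 = 2,613 or 201 × 26 = 5,226 regular requests per arm in a year.

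**Assumed inputs, because the article gives none.** J = 6 to 30 providers; m = 4 or 13 requests per patient; total variance of a request-level value set to 1 and split into provider (vp, 5–10%), provider-by-arm (va), patient (vt) and residual (ve). The calculation is balanced, uses normal quantiles, and refers to the t test.

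**Request as the unit, shared providers.** With N = 201 × m per arm:

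- SE used by the test = √(2 / N)
- true SE = √(2 × (va/J + vt/201 + ve/N)); the common provider effect vp cancels in the difference between arms
- actual type I error = 2 × (1 − Φ(1.96 × SE used / true SE))

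Example with J = 12, m = 13, N = 2,613, vp = 0.10; SE used = √(2 / 2,613) = 0.0277:

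| Further variance | True SE | SE used / true SE | Type I error |
|---|---|---|---|
| none | √(2 × 0.90/2,613) = 0.0262 | 1.05 | 3.9% |
| patient 5% | √(2 × (0.05/201 + 0.85/2,613)) = 0.0339 | 0.82 | 11% |
| provider-by-arm 1% | √(2 × (0.01/12 + 0.89/2,613)) = 0.0485 | 0.57 | 26% |
| provider-by-arm 2%, patient 5% | √(2 × (0.02/12 + 0.05/201 + 0.83/2,613)) = 0.0668 | 0.41 | 42% |
| provider-by-arm 5%, patient 10% | √(2 × (0.05/12 + 0.10/201 + 0.75/2,613)) = 0.0995 | 0.28 | 59% |

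Over J = 6 to 30 and m = 4 or 13:

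- common provider effect only: ratio 1.03–1.05, type I error about 4%
- patient clustering of 5% added: ratio 0.82–0.98, type I error 6–11%
- provider-by-arm variance of 2–5% with patient clustering of 5–10%: ratio 0.20–0.80, type I error 12–69%
- provider-by-arm variance of only 1%: from 7% (30 providers, 4 requests, no patient clustering) to 42% (6 providers, 13 requests, 5% patient clustering)

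**Provider average as the unit, shared providers.** Unpaired SE / paired SE = 1/√(1 − ρ), where ρ is the correlation between a provider's two averages.

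| ρ | Ratio | Type I error |
|---|---|---|
| 0.3 | 1.20 | 1.9% |
| 0.5 | 1.41 | 0.6% |
| 0.7 | 1.83 | 0.03% |
| 0.9 | 3.16 | below 0.01% |

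**If providers were separate by arm.** The request-level SE is 0.12–0.66 of the true one, because vp no longer cancels. An unpaired test on provider averages has a ratio of 1.00 and is valid.

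The request-level figures apply to handling time only. Follow-ups per day are not measured per request.

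**The case against.** No test is named for work efficiency itself; its own section promises only an average per arm. The t or Mann-Whitney rule reaches it through a general sentence that was plainly written with patient outcomes in mind, and the unit of analysis for a log-based outcome is the kind of detail a statistical analysis plan would settle. This lowers the weight of the point but does not remove it: the general rule is headed as covering secondary outcomes, and applied as written it is unsuitable here.

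A reader might infer that the article puts the same small set of providers in both arms. It does not say so. Three centers tell us nothing about how many staff take part, and the Discussion's sentence on management of the control group is compatible with shared or separate staff. Sharing is a strong inference from individual randomization, from GPs following up both arms, and from the absence of any separate team, but it remains an inference.

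A reader might also infer that the error bars are wrong whichever unit is chosen. That is too strong. Provider averages from separate staff would be analysed correctly, and with shared staff and only a common provider effect the request-level test is nearly right. The large request-level errors depend on provider-by-arm variance, for which the article gives no figure. The unpaired test on averages of shared providers is conservative and would not create a false claim of benefit.

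**Conclusion.** The point holds as a minor one. The plan's only named between-group tests for a continuous secondary outcome ignore the clustering of requests within patients and providers, and ignore the pairing that arises if providers serve both arms. The direction depends on the unit: usually too small a standard error for requests, too large for averages of shared providers. The sizes rest on assumed provider numbers, request counts, variance shares and correlations, and should be read as ranges, not as estimates for this trial. The sample size and the primary analysis are untouched.

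**What to change.** In Work efficiency of care providers and in Statistical methods {20a}:

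- State whether the same providers serve both arms, and name the unit of analysis for each index.
- Handling time: compare within provider, using each provider's intervention-minus-control difference with a paired t or signed-rank test and a 95% CI. Alternatively, fit a mixed model on requests with random effects for provider, provider-by-arm and patient.
- Restrict this comparison to regular follow-ups. Table 1 marks abnormal-condition intervention and compliance management as not executed in the control group, so the weighted average over three types does not compare like with like, whatever standard error is used.
- Follow-ups per day: use the paired provider-level comparison.
- Report the number of providers. If there are few, use a small-sample correction or report the outcome descriptively.

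The cost is wording and a little more analysis. Providers already have unique IDs (Data management {19}) and follow-ups are recorded in the system, so no new data are needed. The downside is that intervals will usually be wider than those of a request-level test, which reflects the real information in the data.

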**Fig. 2 Fig2:**
[figure not shown]
System architecture

In this trial, all the interventions will be conducted through the system. The intervention group will gain full access to the system and manage their hypertension under the guidance of the model. The control group will only gain partial access to the system (only for BP measurement) and receive care as usual. Table 1 summarizes all the interventions for each group.

**Table 1 Tab1:** All the interventions for the 2 groups

Intervention category	Execution method in the control group	Execution method in the intervention group
Diagnosis	By physicians (before the trial)	By physicians (before the trial)
Risk assessment	No execution	Conducted by GPs with the assistance of the system; reassessed based on self-monitoring data per week
Hierarchical management	Executed by the system based on patients’ BP values; only adjusted after regular follow-up; no management plans for patients	Executed by the system based on patients’ risk level per week; provide executable management plans to patients
Regular follow-up	Performed by GPs once every 3 months for level 1 patients and once every 2–4 weeks for level 2 patients; no dynamic adjustment	Performed by GPs once every 3 months for level 1 patients and once every 2 weeks for level 2 patients; dynamically adjusted based on patients’ management level
Abnormal condition intervention	No execution	Conducted by GPs; abnormal condition is informed by the system
Compliance management	No execution	Conducted by CMs; compliance is calculated by the system per week
Medication guidance	Provided by GPs during regular follow-up	Provided by physicians or GPs through the system anytime
Lifestyle guidance	Provided by GPs during regular follow-up	Provided by physicians or GPs through the system anytime
Health education	Provided by GPs during regular follow-up	Conducted by CMs through the system, mainly in the form of online materials

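### The two work-efficiency indexes are not like-for-like between the arms, so they cannot support the stated inference about care providers' efficiency

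*Protocol article*

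**What the plan says.** The section on work efficiency of care providers (under Plans for assessment and collection of outcomes {18a}) defines two indexes from the system log.

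- **Follow-ups per day:** "one is the frequency of follow-up in a day, which demonstrates how our system reduces the time cost of a single follow-up".
- **Handling time of a request:** "which means the time duration before a generated follow-up request is handled".

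On request types it says: "The generated follow-up requests can be divided into 3 types: regular follow-up, abnormal attention follow-up, and compliance follow-up". For handling time, "we will calculate time cost for the 3 types of follow-ups respectively, then sum it together with different weights" gives the average. The direction of benefit is stated as "the more follow-up care providers conduct in a day and the less handling time a follow-up request costs, the more effective their work will be". Averages are to be derived "in the entire trial period for the control group and the intervention group, respectively".

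Table 1 sets different follow-up demand by arm. Level 1 patients are followed up every 3 months in both arms. Level 2 patients in the intervention arm are followed up "once every 2 weeks for level 2 patients; dynamically adjusted" according to management level; in controls the interval is 2 to 4 weeks without dynamic adjustment. Table 1 lists abnormal condition intervention and compliance management as not executed in controls.

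Intervention description {11a} defines level 2 in controls as blood pressure not at target. For the intervention arm, the text with Fig. 1 defines it as high cardiovascular risk, reassessed weekly, and adds an extra follow-up when compliance is low.

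**The concern.** An efficiency measure should relate work done to the time or effort it took. The first index counts follow-ups. All follow-ups are generated through the system, so the count depends on how many requests each arm's rules produce. It holds no information on how long one follow-up takes, yet that is the inference the text draws from it.

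The second index does measure time, namely the wait before a request is handled. It then combines three request types, two of which belong to tasks that controls do not receive, so the two arm values are made of different parts.

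Outcomes {12} uses this outcome to validate the model from the care providers' side. A between-arm difference could be reported as a gain or loss in efficiency when it reflects only assigned workload or request mix.

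**Working it through.** **Stated figures.** The protocol gives no numerical target or expected value for work efficiency, so there is none to reproduce. The sample size plays no part here, except that 402 patients allocated 1:1 give 201 per arm.

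**Inputs from Table 1, per patient-year**
- Level 1, both arms: 12/3 = 4 regular follow-ups.
- Level 2, intervention: 52/2 = 26.
- Level 2, control: 52/4 = 13 to 52/2 = 26.

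The protocol does not state the share of patients at level 2, written p below. It is assumed and varied from 0 to 1. Provider speed, number of providers and days worked are taken as equal for the two arms.

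**Step 1: follow-ups per day, equal level mix.** Regular follow-ups per patient-year are 4(1 − p) + 26p = 4 + 22p in the intervention arm. In controls seen 4-weekly they are 4(1 − p) + 13p = 4 + 9p.

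| p | Intervention | Control, 4-weekly | Ratio |
|---|---|---|---|
| 0 | 4 | 4 | 1.00 |
| 0.25 | 9.5 | 6.25 | 1.52 |
| 0.50 | 15 | 8.5 | 1.76 |
| 0.75 | 20.5 | 10.75 | 1.91 |
| 1 | 26 | 13 | 2.00 |

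If controls are seen 2-weekly, the ratio is 1.00 throughout. At p = 0.50 with 4-weekly controls, the daily counts are 201 × 15/365 = 8.26 and 201 × 8.5/365 = 4.68.

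**Step 2: follow-ups that only the intervention arm generates.** Their rate is not stated. At p = 0.50, an assumed 3 per patient-year raises the intervention count by 3/15 = 20%; an assumed 12 raises it by 12/15 = 80%.

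**Step 3: unequal level mix.** The level definitions differ by arm, so the shares need not match. Suppose all controls are at level 2 and 25% of the intervention arm is. The ratio on regular follow-ups is then 9.5/13 = 0.73 (4-weekly controls) to 9.5/26 = 0.37 (2-weekly controls). With all controls at level 2 and seen 4-weekly, the intervention count is the higher only if 4 + 22p > 13, that is p > 9/22 = 41%.

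The count can therefore move either way with no change in how fast anyone works.

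**Step 4: handling time.** Times and weights here are illustrative assumptions, in the order regular, abnormal, compliance.
- Every request waits 24 h, equal weights. Intervention: (24 + 24 + 24)/3 = 24 h. Control: 24/3 = 8 h if absent types count as zero, or 24 h if the weight is rescaled to the one type present.
- Waits of 48, 2 and 24 h, equal weights. Intervention: 74/3 = 24.7 h. Control: 48/3 = 16 h, or 48 h after rescaling.

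In the second example regular requests wait 48 h in both arms, so the only like-for-like comparison shows no difference. The index nevertheless makes controls look faster (16 against 24.7 h) or slower (48 against 24.7 h), depending on how the absent types are treated.

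**The case against.** The strongest counter-arguments, and what stands of each:

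- **Handling time is not set by any schedule.** This stands. A reader might infer that both indexes are fixed by the follow-up timetable. The definition of handling time does not support that; its problem is composition alone. Even the daily count depends on level mix, on alerts and on where controls fall in the 2 to 4 week range. Those, however, are also features of demand and not of efficiency.
- **The direction is not established.** This stands. A reader might infer that the plan is bound to favour the intervention because it creates more work. Eligibility criteria {10} require uncontrolled blood pressure, so many controls may start at level 2, and Step 3 shows that the regular count can then be lower in the intervention arm. The 2.0 is the extreme of the equal-mix range.
- **The two indexes are meant to be read together, and no rule declares efficiency on the count alone.** This is true and softens the point. Joint reading does not make the count a measure of time per follow-up, nor does it restore the missing control components.
- **The weights may be fixed elsewhere, for example as request shares.** Leaving them out of an article is not a fault. With request shares the control value would be defined: it would equal its regular handling time. The arms would still differ in request mix. If the intervention requests split equally over the three types, Step 4 gives 24.7 against 48 h with identical handling of regular requests.
- **Handling time by type is already calculated.** This stands, and it is why the remedy is cheap. The defect lies in the aggregation.

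**Conclusion.** The point holds in this form: the two indexes are not like-for-like between arms and cannot be interpreted as provider efficiency. On the protocol's own intervals, the scheduled daily count differs by a factor of 1.0 to 2.0 at equal provider speed and equal level mix, before any follow-up that only the intervention arm generates. With unequal level shares the ratio can fall below 1 (0.37 to 0.73 in the case shown). Two of the three handling-time components have no control counterpart, whatever the weights.

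A reader might go further and say that the provider-side conclusion will be wrong whichever way it falls. The documents do not show that; they show only that a difference could not be attributed to efficiency. Level shares, rates of extra follow-up, waiting times and weights are all assumptions here. That intervals and tasks differ by arm comes from Table 1, and no view is taken on which follow-up schedule is appropriate.

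Work efficiency is a secondary outcome. The primary outcome, systolic blood pressure, is untouched.

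**What to change.** Reword the outcome and its analysis:

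1. Make the between-arm handling-time comparison on regular follow-up requests only, the one type both arms share. The plan already calculates this by type.
2. Report handling times for abnormal-condition and compliance requests descriptively, in the intervention arm.
3. Do not use the weighted sum for the between-arm comparison.
4. Present follow-ups per day as workload, for example per patient-year and by request type, and remove the statement that it shows a lower time cost per follow-up.

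A direct comparison of time spent per follow-up would be possible only if the log records when each one starts and ends, which the protocol does not show.

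The change uses the same system logs and alters no treatment, visit or data collection. The cost is a change of wording and the loss of a single summary index.
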